### 2.6. Collection, Preparation, and Archiving of Biological Samples

Stool and blood specimens will be collected at the baseline during enrolment at the hospital by the study staff and during follow-up home visits by the field staff following the schedule (Table 1) to evaluate inflammatory and immune markers. Gut barrier function will be assessed using the lactulose rhamnose (LR) permeability test, wherein urine will be collected before, 2 h after, and 5 h after the administration of LR solution to determine the ratio of L:R among the study children. Using blood serum, we will measure C-reactive protein, intestinal fatty-acid-binding protein, lipopolysaccharide, and flagellar (FliC) IgA and IgG levels to measure systemic inflammation, enterocyte death, and the translocation of pathogens. We will monitor gut inflammation by measuring the levels of myeloperoxidase (MPO) and lactoferrin (LF) in stool samples. The panel of 10 inflammatory cytokines (IL-2, -4, -6, -8, -10, -13, -1ß, TNF-α, IFN-γ, IL-17) will be tested in both serum and stool samples. Other major enteric pathogens will be detected in stool using quantitative PCR. All samples will be collected, processed, and stored following the standard operating procedures developed in the study protocol and following the schedule of events (Table 1).

In order to evaluate whether the RLDT could be implemented in a rural primary healthcare hospital in Bangladesh, we will train the hospital staff in the RLDT procedure and certify them. During the screening for enrolment in the INSIGHT study, 225 randomly selected stool samples will be sent to the rural hospital lab to be rescreened with the RLDT by the trained hospital staff, independently. The results will be compared with the RLDT results that were obtained by the INSIGHT study staff for the purpose of enrolling participants. We will determine the level of technical support needed for the RLDT, its ease of use, and its acceptability among the hospital lab staff using a questionnaire.

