## 3. Statistical Considerations

### 3.1. Sample Size and Power

This study’s hypothesis is that the rates of hospitalization (inpatient) will be similar among the NDSD and DS cases. This is a matched set of cases (DS) and controls (NDSD) with two matched controls per case. The second comparison group is the WD group (1:1 matched with case). Based on previous data on the hospitalization rates of shigellosis cases in Mirzapur (obtained via personal communication with [name] et al.), we assume that the probability of hospitalization among the controls will be 20%. Since it is not known, as a general practice, the correlation coefficient for exposure between the matched cases and controls is set to 0.2. If the true odds ratio for hospitalization in the exposed subjects relative to the unexposed subjects is 0.5, we will need to study 123 cases of shigellosis with dysentery with 2 matched controls per case in order to be able to reject the null hypothesis that this odds ratio equals 1 with a probability (power) of 0.8. If the alternative hypothesis is not satisfied, then we will accept the null hypothesis of no difference in hospitalization rates between the cases and controls. The Type I error probability associated with the test of this null hypothesis is 0.05. With an estimated 20% of participants lost to follow-up, we will enroll 148 children each in the DS and WD groups and 296 in the NDSD group (total: 592).

For the RLDT evaluation in the primary healthcare facility, a sample size of 225 (45 subjects with Shigella) achieves 80% power to detect a change in sensitivity from 0.60 to 0.80 using a two-sided binomial test and 100% power to detect a change in specificity from 0.60 to 0.80 using a two-sided binomial test with the target significance level set to 0.05. The actual significance level achieved by the sensitivity test is 0.0336 and that achieved by the specificity test is 0.0397. The prevalence of the disease is ~20%.

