The magnitudes and kinetics of the inflammatory markers will be compared at enrolment and over the follow-up period between DS cases and NDSD cases. Analyses for comparisons of dichotomous outcomes, such as fold increases/decreases in the markers from baseline, will be performed with the chi-square test or Fisher’s exact test if cell counts are sparse. For comparisons of the levels at a specific day between the two groups, a student’s *t*-test will be performed. MPO and LF data will be adjusted for breastfeeding. The data from the cases and their matched controls will be evaluated using paired *t*-tests. Linear regression analysis results will be compared between cases and controls adjusting for anthropometry and cognitive developmental changes, future diarrhea episodes, and antibiotic use in the follow-up period, and sociodemographic risk factors for inflammation.

For the RLDT evaluation at the rural primary healthcare facility, the RLDT results from the hospital staff will be compared with the results from the INSIGHT study staff (gold standard), analyzing sensitivity, specificity, and positive and negative predictive values. We will also use pairwise comparisons with Cohen’s kappa (measuring the agreement between binary outcomes +/− of tests without requiring a gold-standard).

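### Fold change in inflammatory markers is tested as a yes/no outcome with no cut-off, and no scale is stated for the marker t-tests and regression; a continuous log-scale analysis would be more efficient

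*Protocol article*

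**What the plan says.** Aim 3 (section 2.2) concerns gut barrier function, systemic inflammation and gut inflammation. Section 2.6 lists the serum and stool markers: C-reactive protein, intestinal fatty-acid-binding protein, antibody levels, ten cytokines and, in stool, "We will monitor gut inflammation by measuring the levels of myeloperoxidase (MPO) and lactoferrin (LF) in stool samples". Table 1 schedules the stool and blood markers from day 1 to month 12.

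Section 3.2 gives the aim of the marker analysis as "The magnitudes and kinetics of the inflammatory markers will be compared at enrolment and over the follow-up period between DS cases and NDSD cases". It then names these methods:

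- Fold change: "Analyses for comparisons of dichotomous outcomes, such as fold increases/decreases in the markers from baseline, will be performed with the chi-square test". Where cells are sparse, Fisher's test takes its place. The fold that counts as a rise or fall is not stated.
- Levels: "For comparisons of the levels at a specific day between the two groups", a Student's t-test.
- Matched data: "The data from the cases and their matched controls will be evaluated using paired" t-tests.
- Adjusted analysis: "Linear regression analysis results will be compared between cases and controls adjusting for anthropometry and cognitive developmental changes", and for later diarrhea, antibiotic use and sociodemographic factors. MPO and lactoferrin are also adjusted for breastfeeding.

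Neither a log nor a raw scale is stated for any of these. The marker regression does not list the marker's own baseline level. In the same section, the anthropometry regression adjusts for the enrolment Z score and the developmental regression for the baseline test score.

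**The concern.** Fold change is a continuous quantity on a ratio scale. Turning it into yes/no before testing throws away how large each change was, and without a stated cut-off neither the test nor its power is fixed. Fold change also implies a multiplicative scale, which sits uneasily with t-tests whose scale is left open. If concentrations are strongly right-skewed and enter untransformed, a few high values dominate the means and the tests lose power. At stake is Aim 3: a real difference in inflammation between NDSD and DS could be missed because of the method.

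**Working it through.** **No figure to reproduce.** The protocol gives no effect size, SD, cut-off or power for any marker. The check therefore compares methods under stated assumptions.

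**Inputs from the protocol (section 3.1).** Evaluable size: "we will need to study 123 cases of shigellosis with dysentery with 2 matched controls per case", so 123 DS and 246 NDSD. Enrolment is larger: "we will enroll 148 children each in the DS and WD groups and 296 in the NDSD group". The 5% level is stated for hospitalization; two-sided 5% is assumed here for markers. The groups are treated as independent unless noted.

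**Assumptions.** Log-normal markers; a true ratio of geometric means of 1.5 at follow-up and none at enrolment; correlation of 0.4 between log baseline and log follow-up; a two-fold cut; log SD from 0.5 to 1.5.

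**Step 1. Loss from any cut.** √(1/123 + 1/246) = 0.1104. The effect that a t-test on log values detects with 80% power is (1.960 + 0.842) × 0.1104 = 0.309 SD. Cut the same normal log fold change at control quantile q and test the two proportions. The asymptotic relative efficiency is φ(z_q)² / [q(1 − q)].

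| NDSD children above the cut | Relative efficiency | Power of chi-square |
|---|---|---|
| 50% | 0.64 | 60% |
| 30% | 0.58 | 59% |
| 20% | 0.49 | 55% |
| 10% | 0.34 | 45% |
| 5% | 0.22 | 34% |

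The continuous test has 80% power in every row. This step needs a normal log fold change but no value for its SD.

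**Step 2. A two-fold cut.** The SD of log fold change is s√[2(1 − 0.4)] = 1.095s. Power of the continuous comparison is Φ(0.405 / (1.095s × 0.1104) − 1.960), where 0.405 = ln 1.5. For s = 1.0 this is Φ(3.35 − 1.96) = 92%. The proportions above two-fold are 1 − Φ(0.693/1.095) = 26% in NDSD and 1 − Φ((0.693 − 0.405)/1.095) = 40% in DS. Simulated power:

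| Log SD | Two-fold cut, chi-square | Mean log fold change, t-test | Loss |
|---|---|---|---|
| 1.0 | 74% | 91% | 17 |
| 1.3 | 52% | 72% | 20 |
| 1.5 | 43% | 61% | 18 |

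The closed form for the continuous test gives 92%, 73% and 61%, within about one point of the simulation.

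**Step 3. Levels on one day.** Log-scale power is Φ(0.405 / (s × 0.1104) − 1.960). For s = 1.0 this is Φ(3.67 − 1.96) = 96%; for 1.3 and 1.5 it is 81% and 69%. Simulated power:

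| Log SD | Student's t, raw | Student's t, log |
|---|---|---|
| 1.0 | 84% | 96% |
| 1.3 | 51% | 82% |
| 1.5 | 37% | 68% |

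At log SD 0.75 or below, both tests have about 99% power or more for a ratio of 1.5. Part of that is a ceiling: with the effect set for 80% power on the log scale, the raw test has 75% at log SD 0.5 and 70% at 0.75. Under the null, the raw test rejected in 4% to 5% of runs.

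**Step 4. Do the paired t-tests avoid this?** Take each case against the mean of its two controls, with an assumed within-set correlation of 0.2. Raw values give about 86%, 46% and 27% power at log SD 1.0, 1.3 and 1.5; log values give 98%, 88% and 77%. The paired tests keep the data continuous but depend on scale in the same way.

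**Step 5. Is baseline adjustment a plain substitute?** If the ratio of 1.5 is already present at enrolment and persists, a log-baseline-adjusted model estimates exp[(1 − 0.4) × 0.405] = 1.28. Its power is then about 65%, 45% and 36% at log SD 1.0, 1.3 and 1.5. It answers a different question from the unadjusted level comparison.

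**The case against.** Several stronger readings are tempting, and the document does not support them.

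- A reader might infer that Aim 3 rests on the chi-square and day-by-day t-tests alone, so that continuous information is discarded. It is not: paired t-tests and linear regression stand beside them, and fold change is named only as an example of a dichotomous outcome.
- A reader might infer that raw concentrations will be analysed. The article neither states nor excludes a log transformation, and that detail may sit in a full protocol or analysis plan not shown. If values are logged, the loss in steps 3 and 4 disappears.
- A reader might take the markers to be right-skewed as a fact. The article says nothing about their distributions. Skewness is an assumption here, and at modest skewness the raw t-test loses little.
- A reader might conclude that the tests are invalid, or that a non-significant marker result will be read as equality. Type I error holds in the simulation, and the rule in section 3.1 about accepting the null is written for hospitalization only.
- A reader might want a baseline-adjusted model as the single replacement. DS and NDSD are not randomised; they are defined by visible blood in stool and may differ at enrolment, so step 5 applies.

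What remains does not rest on silence: a test of dichotomised fold change is a stated choice, and it is less efficient than a continuous test of the same quantity. The unstated scale matters because the other planned analyses inherit it.

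**Conclusion.** The point holds in this limited form. Dichotomising fold change costs about 17 to 20 points of power under the assumed two-fold cut and log SD 1.0 to 1.5. It costs about 20 points at the best possible cut when the continuous test has 80% power, and more at extreme cuts. The loss from t-tests on levels is conditional: about 12, 31 and 31 points at log SD 1.0, 1.3 and 1.5 if strongly skewed values are analysed raw, and none if they are logged. The exact sizes rest on log-normality, a ratio of 1.5, a correlation of 0.4 and 123 against 246 evaluable children. This is a matter of efficiency and clarity, not validity, and it does not undermine the marker analysis as a whole.

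**What to change.** In section 3.2, or in the analysis plan:

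1. State that markers are analysed as continuous on the log scale in the t-tests, paired t-tests and regression, with ratios of geometric means and 95% confidence intervals.
2. Replace the chi-square or Fisher test of fold change by a comparison of mean log fold change. Keep the proportion above a stated fold cut as description.
3. If wanted, add a model for change after enrolment with log baseline as covariate. Label it as a different question from the unadjusted level comparison, because the groups may already differ at enrolment.

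The cost is wording only; no new data are needed. There are two downsides. Values below the assay limit need a stated rule before logging, and results are ratios rather than differences in concentration.

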### 2.2. Aims

The objectives of this study are to (1) determine the morbidity, risk of hospitalization, and mortality associated with NDSD cases; (2) study the impact of NDSD on the nutritional status and cognitive development of children; (3) understand the impact of NDSD on gut barrier function, systemic inflammation, and gut inflammation in children; (4) determine the Shigella isolates’ resistance to commonly used antibiotics using disk diffusion tests and E-strips; and (4) evaluate if the RLDT could be applicable for the detection and treatment of shigellosis cases in the low-resource clinical settings of a rural primary healthcare facility. The data from aims (1) to (3) will be compared between the NDSD group and the other two groups, DS and WD.

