### 3.2. Statistical Analyses

The indicators of severity and symptoms determined by the morbidity indicators, hospitalization, and diarrheal disease score between the cases and controls at baseline (i.e., upon enrolment) will be evaluated using conditional logistic regression adjusting for sex and other confounding factors. The impact of the initial shigellosis or WD episode on the future morbidity, hospitalization, and mortality of the children, during the follow-up period of 12 months for the NDSD and DS groups or 3 months for the WD group, will be analyzed accounting for the confounding factors. Any antibiotic use during the follow-up period will be recorded and considered during analysis. Initially, bivariate conditional logistic regression models will be developed considering each one of the sociodemographic factors for the risk of shigellosis to select the variables for adjustment in the multivariable model.

The Z scores of all anthropometric measurements of the cases and their matched controls at different time intervals will be compared using paired *t*-tests. We will perform linear regression analyses comparing the baseline Z scores and changes in the Z scores from enrolment to the 3- or 12-month follow-up assessment, adjusting for the enrolment Z score, the duration of the follow-up period, sociodemographic covariates, antibiotic use, future diarrhea episodes, and any hospitalization in the follow-up period, using jack-knife estimates of standard error [26].

The same analytic techniques will be used for evaluating the data from the Bayley and WPPSI scales by comparing both the Z scores and age-adjusted composite scores of all developmental domains in the unadjusted model. In the multivariable-adjusted liner regression model, we will adjust specific baseline test scores for each domain and any other related sociodemographic variables that are significantly different between the groups at baseline, significantly different between the children lost to follow up and the tested children, or significantly associated with developmental outcome measures, e.g., socioeconomic status, sex, mother’s education, HOME assessment result, etc. Five behavioral outcomes will be summed up as total scores and will be used in a similar analysis. Sensitivity and mediation analyses will also be conducted using a Structural Equation Model (SEM) [27] to explore the underlying mechanisms or processes influencing the outcomes.

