## Figures and Tables

**Figure 1 microorganisms-12-01677-f001:**
[figure not shown]
Enrolment flow chart.

**Table 1 microorganisms-12-01677-t001:** Schedule of events.

Study Day/Month (M)	1	3	5	9	14	M1	M2	M3	M4	M5	M6	M7	M8	M9	M10	M11	M12
Enrolment	X																
* Morbidity	X	X	X	X	X	X	X	X	X	X	X	X	X	X	X	X	X
* Stool collection for analysis of microbiology	X	X	X	X	X	X	X	X	X	X	X	X	X	X	X	X	X
Sociodemographic, sanitation, and hygiene questionnaire assessments		X									X						
Urine L:R ratio measurement		X			X			X			X						X
Stool collection for analysis of inflammatory/immune markers	X	X	X	X	X	X		X			X			X			X
Blood collection for analysis of inflammatory/immune markers	X			X		X		X			X			X			X
Anthropometry measurements	X				X	X	X	X	X	X	X	X	X	X	X	X	X
Bayley or WPPSI assessment		X						X									X
HOME assessment		X															

“X” marked the time points of collecting data and samples. * Morbidity data and stool samples will be collected every other day following the baseline visit until day 14 and then two days per week until the participant with DS or NDSD is negative for Shigella. Once their stool has tested negative for Shigella, morbidity data will be collected during home visits twice a week and stool samples will be collected as per the study schedule.

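### The marker analyses for aim 3 are named day by day: as stated they do not test kinetics or give one group comparison per marker, so isolated significant marker-days cannot support the aim on their own

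*Protocol article*

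**What the plan says.** Aim 3 in section 2.2 is to "understand the impact of NDSD on gut barrier function, systemic inflammation, and gut inflammation in children". The same section promises that aims 1 to 3 will compare NDSD with both DS and WD.

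For the markers, section 3.2 says that magnitudes and kinetics "will be compared at enrolment and over the follow-up period between DS cases and NDSD cases". It then names four methods:

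- "For comparisons of the levels at a specific day between the two groups", it says "a student’s *t*-test will be performed".
- Dichotomous outcomes, such as fold change from baseline, get a chi-square or Fisher's exact test.
- Cases and their matched controls are compared by paired t-tests.
- A linear regression is adjusted for growth and developmental change, later diarrhea, antibiotic use and sociodemographic factors. No repeated-measures structure or group-by-time term is mentioned.

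Section 2.6 lists the markers and says that a panel of 10 cytokines "will be tested in both serum and stool samples". Table 1 gives the dates in separate rows for urine, blood and stool, for example "Stool collection for analysis of inflammatory/immune markers".

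For growth, section 3.2 says: "The Z scores of all anthropometric measurements of the cases and their matched controls at different time intervals will be compared using paired" t-tests. It adds adjusted regressions of the change in Z score to 3 or 12 months.

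**The concern.** The stated question and the stated methods do not match. Kinetics means the course of a marker over time within a child, and whether that course differs between groups. A t-test on one day uses none of the child's other measurements, and a series of such tests does not become a test of the course. A fold change uses the baseline and one later value, then discards information by dichotomising. The paired t-test uses the matching but still works on one value per child. The regression could in principle be longitudinal, but nothing in its description says so.

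The result is that no single comparison answers, for a given marker, whether NDSD differs from DS over follow-up. What remains is a large grid of marker-by-day results. Aim 3 stands beside aims 1 and 2, and the article ties the study to whether treatment guidance should be revisited. If the grid is read cell by cell, some cells will look significant by chance, and nothing in the named analyses separates these from real differences.

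**Working it through.** The article gives no number of tests and no error rate for these comparisons, so there is no figure to reproduce. The count below is built from its own lists.

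**Markers (section 2.6)**
- Stool: myeloperoxidase, lactoferrin and 10 cytokines = 12.
- Serum: C-reactive protein, intestinal fatty-acid-binding protein, lipopolysaccharide, FliC IgA, FliC IgG and 10 cytokines = 15. It is 16 if lipopolysaccharide is read as separate IgA and IgG.
- Urine: L:R ratio = 1.
- Total: 12 + 15 + 1 = 28, or 29.

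**Dates (Table 1)**
- Stool markers: days 1, 3, 5, 9, 14 and months 1, 3, 6, 9, 12 = 10, of which 7 fall by month 3.
- Blood markers: days 1, 9 and months 1, 3, 6, 9, 12 = 7, of which 4 fall by month 3.
- Urine: days 3, 14 and months 3, 6, 12 = 5, of which 3 fall by month 3.

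**Assumptions**
- Every marker is tested once on every scheduled day.
- Each test is two-sided at 0.05. Section 3.1 attaches that level to the hospitalization hypothesis ("The Type I error probability associated with the test of this null hypothesis is 0.05") and to the RLDT tests, not to the markers.
- The L:R ratio is analysed like the other markers, and WD children follow Table 1 up to month 3.

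**Tests = markers × dates; expected false positives = 0.05 × tests, if the groups do not differ**
- DS versus NDSD: 12 × 10 + 15 × 7 + 1 × 5 = 120 + 105 + 5 = 230. With 16 serum markers: 120 + 112 + 5 = 237. Expected: 0.05 × 230 = 11.5 to 0.05 × 237 = 11.85.
- NDSD versus WD: 12 × 7 + 15 × 4 + 1 × 3 = 84 + 60 + 3 = 147. With 16 serum markers: 84 + 64 + 3 = 151. Expected: 7.35 to 7.55.

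Fold-change tests would come on top.

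**Effect of correlation.** The expected count does not depend on correlation between tests, but the chance of at least one false positive does. Two simulations of DS versus NDSD, with assumed correlations, give the range:
- Correlations of 0.3 to 0.7 between markers and between days, with stool, serum and urine treated as independent (237 tests): the chance of at least one runs from 0.9998 down to 0.92. The median number of false positives falls from 11 to 7.
- One common correlation across all 230 tests: 0.92 at correlation 0.5 and 0.43 at 0.8.

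**Anthropometry.** There are 4 measures (section 2.4) and 14 dates (days 1, 14 and months 1 to 12), 5 of them by month 3. DS versus NDSD: 4 × 14 = 56 tests, 0.05 × 56 = 2.8 expected. NDSD versus WD: 4 × 5 = 20 tests, 1.0 expected. With an assumed correlation of 0.5 between measures and 0.8 to 0.95 between dates, the chance of at least one among the 56 is 0.51 down to 0.31.

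**The case against.** The strongest reply is that this is a condensed article whose analysis plan is not shown. A multiplicity rule, a lead marker or a lead day may be set there, so their absence here is no error. That stands, and the point does not rest on it. It rests on the methods the article does name, which do not match the comparison it says it will make.

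Two further replies also stand. The t-test sentence says which test to use when a day is compared; it does not say that every marker is tested on every day, so 230 is a ceiling under an assumption and not a plan. The day-specific tests are also not the only analysis, since paired tests, fold changes and an adjusted regression are listed. These do not close the gap, because none is described as using a child's whole series or as comparing the groups' courses.

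For anthropometry the reply largely succeeds: adjusted regressions of change to 3 or 12 months are already planned, and monthly Z scores in one child are likely to be highly correlated.

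A reader might infer that aim 3 is almost certain to report a false impact. The documents do not support that. It would need all groups to be truly alike and any one significant marker-day to count as an impact, and the article sets no such rule. Under high common correlation the chance of even one false positive is 43%. A reader might also infer that all tests run at an unadjusted 0.05, or that each contrast has 230 tests. The first is not stated, and the second is wrong for WD, whose follow-up ends at 3 months.

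**Conclusion.** The point holds as a mismatch between question and method. Section 3.2 promises a comparison of marker kinetics between DS and NDSD, and none of the methods it names, as described, tests kinetics or yields one group comparison per marker. Its size depends on how the marker-by-day grid is used. With all markers tested on all scheduled days at 0.05, about 11 to 12 chance findings are expected for DS versus NDSD and about 7 to 8 for NDSD versus WD, if the groups do not differ. Testing every cell and using 0.05 are assumptions. Isolated significant marker-days could therefore not support aim 3 on their own. The markers are the stronger part; for anthropometry, only a statement of which planned analysis leads is needed. This should be changed, but it does not touch the hospitalization hypothesis on which the study is sized.

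**What to change.** In section 3.2, make the main marker analysis one repeated-measures mixed model per marker, on a suitable scale such as log. Include group, time and group-by-time, with random effects for child and matched set. Use all scheduled time points for DS versus NDSD and those up to month 3 for NDSD versus WD. Take one overall group test per marker and contrast, for instance the joint test of the group and group-by-time terms, and read the group-by-time term as the comparison of kinetics. Control the false discovery rate across the roughly 28 markers within each contrast, for example by Benjamini-Hochberg. Show day-specific differences as estimates with confidence intervals.

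For anthropometry, state that the planned 3- and 12-month regressions are the main tests and that comparisons at other dates are descriptive.

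The cost is revised wording and somewhat more complex programming, on data already scheduled for collection. The downside is that fewer individual marker-days will be called significant.
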